### Web-Based Module Content

Both e-CBT modules and in-person CBT sessions are designed to instill constructive and balanced coping strategies in the participants. During the program, we focus on essential thinking and behavioral skills to help patients become more engaged in day-to-day activities. The sessions focus on the connection between thoughts, behaviors, emotions, physical reactions, and the environment. In addition, we will evaluate negative beliefs and thought processes and their relationships with depression. Our goal is to adjust negative thinking so that participants can think about and adapt to the things that are happening to them. This allows them to adjust the way they behave and think about their problems in a way that is not as negative and replaces those thoughts and behaviors with potentially more realistic and productive ones. The 12 e-CBT sessions will follow the themes listed below:

*What is depression?* Provides expectations for the course and introduces the concepts of CBT and depression.*5-part model:* Introduces the 5-part model (how situations, thoughts, feelings, physical reactions, and behaviors are connected and how they interact with each other).*Situation, thoughts, feelings, physical reactions, and behaviors:* Provides further detailed exploration of the 5-part model and how changes in an area affect the other parts.*Rating feelings and thought records:* Highlights the first 3 columns of a thought record (a tool used to help understand the connection between feelings, behaviors, and thoughts), which are situation, feelings, and automatic thoughts associated with the situation.*Automatic thoughts:* Explains the role of automatic thoughts and how they influence feelings. Provides ways to identify thoughts and specifically identify the most dominant thoughts in stressful situations.*Evidence:* Focusing on columns 4 and 5 of the thought record, which are designed to help gather evidence that supports or does not support the identified automatic thought.*Alternative and balanced thinking:* Focus on the final 2 columns of the thought record that reflect on the evidence columns to help find alternative and more balanced views of the situation. The final column has the patient rerate their feelings based on the completion of the thought record.*Experiments:* Explains the importance of conducting experiments to believe the alternative and balanced thoughts from the thought record to initiate changes in negative thinking patterns.*Action plans:* Centered around using the thought record to identify a problem that needs to be solved and providing a framework for creating a plan for solving the problem.*Strategies for stressful situations:* Overview of helpful strategies that can be used in stressful situations, including distraction activities and helpful breathing techniques.*Activity scheduling:* Explains activity records and how using one can inform the patient on their mood changes and help reinforce scheduling positive activities into their day.*Review:* Summarizes the main concepts of CBT and the tools and skills that the patient should continue to practice beyond completion of the final session.

### Training

All therapists are research assistants hired by the principal investigator. All therapists undergo training in psychotherapy and receive additional training from a psychiatrist from the research team before any interaction with participants. During this training, therapists complete feedback on practice homework, which is reviewed by a psychiatrist from the research team to ensure adequate quality of work. All therapists are supervised by the lead psychiatrist, who is an expert in electronically delivered psychotherapy [23,24]. Feedback is always reviewed by the lead psychiatrist, before submission to the participants.

### Outcome Evaluation

The primary outcomes that will be measured include changes in symptoms of depression based on the following clinically validated symptomology questionnaires: Patient Health Questionnaire-9 (PHQ-9) and the Quick Inventory of Depressive Symptomatology Questionnaire [33,34]. An additional measurement of quality of life change will be made based on the Quality of Life and Enjoyment Questionnaire [35]. All questionnaires were shown to be reliable and highly valid. Questionnaires will be collected directly through OPTT before treatment (baseline), after session 6, after the final session (week 12), and after a 6-month follow-up. Participants will not be offered incentives to increase the completion of the questionnaires. OPTT will collect use statistics (ie, log-ins per day and amount of time spent logged in) to help better understand the relationship between engagement and treatment outcomes.

Through the focus groups, health care providers will be asked about the feasibility of providing the electronic-delivered psychotherapy program and how it compares with in-person psychotherapy delivery. They will be asked to make their judgments based on variables such as time commitment, connectedness to patients, and benefits and drawbacks. From the focus group interviews with the participants, personal, social, and cultural factors (eg, gender, sexuality, background, supportive resources, and structural or social barriers) will be extracted using an interpretive phenomenological analysis approach. In addition, any adverse events and adherence to the intervention will be reported.

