### Data Analysis

This is a confirmatory study with previously established objectives and analyses. Initially, all data are examined for missing, nonsensical, and outlying variables. Missing data are treated as missing and not imputed (ie, will be analyzed on a per-protocol basis). The participants in this study were intentionally oversampled to account for dropouts or withdrawals. On the basis of previous research, an anticipated dropout rate of up to 30% was factored in. Using the PHQ-9 as the primary outcome, a 30% change is considered clinically significant. Therefore, a sample size of 55 participants in each arm of the study would be sufficient for detecting significant results with *P*=.05 and a power of 0.95. Data collection occurs at baseline (preintervention), in the middle of the study (week 6), immediately after the intervention (week 12), and at a 6-month follow-up. Using Mann-Whitney *U* tests, demographic information can be compared between participants who complete the program and those who withdraw prematurely in the hope of identifying possible differences between the two. Moreover, an intention-to-treat analysis will be conducted to evaluate the clinical effects of treatment on participants who withdraw prematurely. Linear regression analysis (for continuous outcomes) and binomial regression analysis (for categorical outcomes) will be used to identify variables associated with the outcome measures (PHQ-9, Quick Inventory of Depressive Symptomatology Questionnaire, and Quality of Life and Enjoyment Questionnaire). This will occur over the 4 measurement time points while controlling for demographic variables, including age and gender. In addition, a comparative analysis between both groups’ questionnaire scores will be conducted at all data collection time points using group and paired two-tailed *t* tests.

Other quantitative measures for the e-CBT group will be gathered by extrapolating recorded information directly through the OPTT platform (eg, the number of log-ins per day and the amount of time spent logged in). Qualitative measurement analyses will be conducted to inquire about the role of personal, social, and cultural factors in enabling or constraining the use of e-CBT. The findings will identify factors related to the utility, feasibility, and accessibility of e-CBT from the perspectives of users and providers. Interpretive qualitative methods are ideal for gathering in-depth descriptions of user experience and meaning.

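### The article names two primary questionnaires in one section and one in another, tests the arms at every visit, and names no deciding comparison for a study it calls confirmatory

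*Protocol article*

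**What the plan says.** All of this is in the Methods of the protocol article.

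- **Outcome Evaluation, primary outcomes.** The text reads "The primary outcomes that will be measured include changes in symptoms of depression based on the following clinically validated symptomology questionnaires" and then names two instruments: "Patient Health Questionnaire-9 (PHQ-9) and the Quick Inventory of Depressive Symptomatology Questionnaire". Quality of life ranks lower: "An additional measurement of quality of life change will be made based on the Quality of Life and Enjoyment Questionnaire".
- **Data Analysis, sample size.** Only one instrument is called primary: "Using the PHQ-9 as the primary outcome, a 30% change is considered clinically significant". From this the section derives 55 per arm at P=.05 and power 0.95, with dropout of up to 30% factored in.
- **Data Analysis, status of the study.** "This is a confirmatory study with previously established objectives and analyses".
- **Data Analysis, visits and tests.** "Data collection occurs at baseline (preintervention), in the middle of the study (week 6), immediately after the intervention (week 12), and at a 6-month follow-up". The comparison of both groups' "questionnaire scores will be conducted at all data collection time points using group and paired two-tailed" t tests follows. Regressions of all three questionnaires over the four visits are also planned.
- **Study Design and the abstract's Objective.** The hypothesis is that e-CBT gives results comparable with in-person CBT on symptoms and quality of life. No margin is given.

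No section names a primary time point or says whether one or both depression questionnaires must agree.

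**The concern.** A confirmatory study needs one result, or a stated combination of results, that decides its hypothesis. Here the two sections disagree on whether the Quick Inventory is primary, and the article commits to testing at every visit without saying which visit counts. If the two questionnaires or the visits point in different directions, the text does not say which governs.

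The open choice works in both directions. The hypothesis is comparability, but the planned tests are two-tailed tests for a difference. One significant result among several could be presented as a difference between the arms. One nonsignificant result among several could be presented as showing that they are comparable.

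**Working it through.** **1. The plan's own figure.** At two-sided 0.05 and power 0.95, the standardised difference that n per arm can detect is d = (1.960 + 1.645) × √(2/n).

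- n = 55: d = 3.605 × √(2/55) = 0.687.
- n = 38 (55 × 0.70 = 38.5, rounded down, for 30% dropout): d = 3.605 × √(2/38) = 0.827.

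The article gives no SD and no baseline PHQ-9, and does not say whether the 30% change is within or between arms, so 55 can be neither reproduced nor refuted. If the 30% is read as a between-arm difference, an assumed baseline mean of 12 to 18 and SD of 4 to 7 give 15 to 99 per arm before dropout and 22 to 142 after dividing by 0.70. The figure of 55 lies inside that range. The point here does not depend on it.

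**2. Counting the candidate deciding tests.** Two questionnaires called primary × three post-baseline visits (week 6, week 12, 6 months) = 6 between-group comparisons. Left out are the baseline comparisons (not efficacy tests), quality of life (not called primary), the paired tests and the regressions.

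**3. Chance of at least one false difference among the six.** Assume that each is tested at two-sided 0.05 and that the arms truly do not differ. If independent: 1 − 0.95⁶ = 0.265. The tests are in fact correlated and the article gives no correlations, so a range was simulated (400,000 draws of multivariate normal test statistics). The correlation between different questionnaires at different visits was taken as the product of the two values.

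| Assumed correlation between questionnaires | Assumed correlation between visits | At least one P<.05 |
|---|---|---|
| 0 | 0 | 26.5% (formula) |
| 0.6 | 0.4 | 22.1% |
| 0.8 | 0.5 | 19.0% |
| 0.8 | 0.7 | 16.6% |
| 0.9 | 0.8 | 13.5% |

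**4. Chance of at least one nonsignificant result when the arms do differ.** Assume the same true d at all six tests, with correlations of 0.8 between questionnaires and 0.5 between visits. For one named test at d=0.5 and n=55, the expected test statistic is 0.5 × √(55/2) = 2.62. The chance of falling below 1.96 is Φ(1.96 − 2.62) ≈ 25%.

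| True d (assumed) | n per arm | One named test nonsignificant | At least one of six nonsignificant |
|---|---|---|---|
| 0.5 | 55 | 25% | 58% |
| 0.5 | 38 | 41% | 77% |
| 0.687 | 55 | 5% | 17% |
| 0.687 | 38 | 15% | 41% |

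**5. Cost of the alternatives at d=0.687.**

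- One named test at 0.05: 55 per arm keeps its stated power of 0.95.
- Two primary tests at 0.025 each: power with 55 per arm is 0.91, and about 64 analysed per arm are needed for 0.95.
- Six tests at 0.05/6 = 0.0083: power with 55 per arm is 0.83, and about 78 analysed per arm are needed for 0.95.

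**The case against.** The strongest reply is that the PHQ-9 phrase sits inside the sample-size reasoning. Sizing a trial on one of two primary measures is common and does not demote the other. That reading is possible, but it leaves two primaries and no statement of how they jointly decide. The two sections still need to be reconciled.

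A second reply is that ranking visits and controlling multiplicity usually belong in an analysis plan, which is not shown. On its own, silence on those details would not be a finding. But the article itself describes the primary outcome in two ways, calls the study confirmatory, and commits to between-group tests at every visit.

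Third, a false significant difference counts against a hypothesis of comparability, so a familywise error rate describes only one direction of harm. This stands, and it is why step 4 is needed alongside step 3.

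Some stronger readings are tempting but not supported:

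- **That the plan tests every comparison at 0.05.** P=.05 appears only in the sample-size sentence. The sentence on t tests gives no level.
- **That there are nine primary tests, with a 37% error rate if independent.** This counts quality of life, which the article calls an additional measurement although it appears in the hypothesis.
- **That baseline comparisons between arms should go.** Participants choose their arm, so real baseline differences are to be expected and comparing them is informative. Self-selection also makes the exact no-difference assumption in step 3 an idealised reference.

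**Conclusion.** The point holds in this form: Outcome Evaluation and Data Analysis conflict on whether there are two primary questionnaires or one. A study described as confirmatory also plans between-group tests at all visits with no deciding visit and no rule for disagreement.

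The sizes are conditional. The 14-22% for a false difference rests on an assumed 0.05 level per test and assumed correlations, with 26.5% as the independent-test figure. The 58% against 25% for a nonsignificant result rests on those assumptions and on a true d of 0.5 throughout. Confidence is high on the conflict in wording and lower on any single percentage.

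A reader might infer that the authors intend to pick the favourable result, or that the 55 per arm is wrong. The document supports neither. It shows only that the choice is left open.

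**What to change.** - **Name one primary endpoint:** change in PHQ-9 from baseline to week 12. This is the measure already used for sizing, taken at the end of treatment. Another single time point would also resolve the defect if declared in advance.
- **Make the rest secondary and supportive:** the Quick Inventory, quality of life, and the week 6 and 6-month results.
- **Align the wording** of Outcome Evaluation and Data Analysis. If both depression questionnaires are to stay primary, state whether one or both must succeed and at what level each is tested.
- **Date the choice.** Fix it before the arm comparison is seen, or disclose when it was made. The article appeared in June 2021, and its abstract says that data collection was due to finish by March 2021 and that regression analyses were still under way. A choice made at that stage of an open-label study may already be post hoc.
- **Multiplicity control of the secondary outcomes** (Holm or a fixed order) is optional. It limits false claims of a difference but does not itself support a claim of comparability.
- **Keep the baseline comparisons.**

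The cost is a change of wording plus a statement of timing. No extra patients are needed, and the 55 per arm is unaffected by naming a single test.

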### Ethics and Data Privacy

All procedures have been approved by the Queen’s University HSREB. For privacy purposes, participants are only identifiable by an ID number on the platform, and hard copies of the consent forms with participants’ identities are stored securely on site and will be destroyed 5 years after study completion. Participants’ data are only accessible by the care providers directly assigned to that participant, and only anonymized data are provided to the analysis team members. Participants have the option to withdraw from the study at any point and request for their data to be removed from the analysis. However, as the collected data are considered a medical record, it will not be permanently deleted for 10 years after treatment.

The web-based platform used for the study (OPTT) is Health Insurance Portability and Accountability Act, Personal Information Protection and Electronic Documents Act, and Service Organization Control-2 compliant. In addition, all servers and databases are hosted in the Amazon Web Service Canada cloud infrastructure, which is managed by Medstack to ensure that all provincial and federal privacy and security regulations are met. OPTT does not collect any identifiable personal information or internet protocol addresses for privacy purposes. OPTT only collects anonymized metadata to improve its service quality and provide advanced analytics to the clinician team. OPTT encrypts all data, and no employees have direct access to participants’ data. All encrypted backups are kept in the S3 storage that is dedicated to Queen’s University, located in Kingston, Ontario, Canada.

### Data Analysis

This is a confirmatory study with previously established objectives and analyses. Initially, all data are examined for missing, nonsensical, and outlying variables. Missing data are treated as missing and not imputed (ie, will be analyzed on a per-protocol basis). The participants in this study were intentionally oversampled to account for dropouts or withdrawals. On the basis of previous research, an anticipated dropout rate of up to 30% was factored in. Using the PHQ-9 as the primary outcome, a 30% change is considered clinically significant. Therefore, a sample size of 55 participants in each arm of the study would be sufficient for detecting significant results with *P*=.05 and a power of 0.95. Data collection occurs at baseline (preintervention), in the middle of the study (week 6), immediately after the intervention (week 12), and at a 6-month follow-up. Using Mann-Whitney *U* tests, demographic information can be compared between participants who complete the program and those who withdraw prematurely in the hope of identifying possible differences between the two. Moreover, an intention-to-treat analysis will be conducted to evaluate the clinical effects of treatment on participants who withdraw prematurely. Linear regression analysis (for continuous outcomes) and binomial regression analysis (for categorical outcomes) will be used to identify variables associated with the outcome measures (PHQ-9, Quick Inventory of Depressive Symptomatology Questionnaire, and Quality of Life and Enjoyment Questionnaire). This will occur over the 4 measurement time points while controlling for demographic variables, including age and gender. In addition, a comparative analysis between both groups’ questionnaire scores will be conducted at all data collection time points using group and paired two-tailed *t* tests.

Other quantitative measures for the e-CBT group will be gathered by extrapolating recorded information directly through the OPTT platform (eg, the number of log-ins per day and the amount of time spent logged in). Qualitative measurement analyses will be conducted to inquire about the role of personal, social, and cultural factors in enabling or constraining the use of e-CBT. The findings will identify factors related to the utility, feasibility, and accessibility of e-CBT from the perspectives of users and providers. Interpretive qualitative methods are ideal for gathering in-depth descriptions of user experience and meaning.

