### Participants

Patients (N=110; 55 e-CBT participants and 55 in-person CBT participants) aged between 18 and 65 years will be recruited from Queen’s University from the outpatient psychiatry clinic at both the Kingston Health Sciences Center sites (Hotel Dieu Hospital and Kingston General Hospital) as well as from Providence Care Hospital located in Kingston, Ontario, Canada. Additionally, family doctors, physicians, clinicians, and self-referrals will be accepted. Once informed consent is provided, a psychiatrist from the research team will evaluate participants through a secure video appointment to make or confirm a diagnosis of MDD using the Diagnostic and Statistical Manual of Mental Disorders, 5th edition [31].

The inclusion criteria for the study are as follows: aged at least 18 years at the start of the study, diagnosed with MDD according to Diagnostic and Statistical Manual of Mental Disorders, 5th edition by an attending psychiatrist from the research team, competence to consent to participate, ability to speak and read English, and consistent and reliable access to the internet. Exclusion criteria are as follows: active psychosis, acute mania, severe alcohol or substance use disorder, and/or active suicidal or homicidal ideation. If a participant is receiving another form of psychotherapy, they will also be excluded from the study to avoid any confounding effect on the efficacy of this e-CBT program. Participants are eligible for the study if they are receiving pharmacotherapy. However, they must be receiving the same drug and dosage for the duration of the study. If eligible for the study, participants will choose between the e-CBT program (n=55) or the in-person CBT offered individually through this program at Hotel Dieu Hospital (n=55).

During the informed consent process, all participants will be explained that this program is not a crisis resource and that they will not always have access to their therapist. In the case of an emergency, participants will be directed to the proper resources (eg, emergency department or crisis lines), and this event will be reported to the principal investigator of the study. The reasoning behind having a nonrandomized design and allowing patients to choose their treatment is to mimic a real-world setting in which patients have autonomy in their treatment decisions. We recognize that this could be a limitation of this study. We plan to conduct a randomized controlled trial in the future.

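### The Data Analysis section treats leaving missing data unimputed as a per-protocol analysis, describes intention-to-treat as an analysis of withdrawals, and does not say which analysis is primary

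*Protocol article*

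**What the plan says.** All the relevant statements but one stand in a single paragraph of the protocol article, under Data Analysis.

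- Missing data: "Missing data are treated as missing and not imputed (ie, will be analyzed on a per-protocol basis". The rule covers all data and has no exception.
- Dropout: "an anticipated dropout rate of up to 30% was factored in". The stated remedy is a larger sample: "The participants in this study were intentionally oversampled to account for dropouts or withdrawals".
- Sample size: "a sample size of 55 participants in each arm of the study would be sufficient", for a P value of .05 and power of 0.95.
- Second analysis, introduced as an addition: "an intention-to-treat analysis will be conducted to evaluate the clinical effects of treatment on participants who withdraw prematurely".
- Methods: linear and binomial regression over the four measurement times, and a between-group comparison at every time point by "group and paired two-tailed" t tests.
- Check on dropout: completers and early withdrawals are compared on demographic information only.

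The remaining statement is under Participants, where allocation is by preference: "participants will choose between the e-CBT program (n=55) or the in-person CBT". The paragraph calls the study confirmatory with its analyses already established, yet names neither analysis as primary.

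**The concern.** Two terms are used wrongly, and the main comparison depends on both.

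Not imputing is a decision about data handling. Per-protocol is a choice of analysis set, based on adherence to treatment. A participant may attend every session and miss a questionnaire, or stop therapy and still complete one. The rule as written classifies neither.

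Intention-to-treat means that everyone enrolled is analysed in the arm they entered. Read literally, the article's description is instead a look at the subgroup who withdraw.

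The study hypothesis is that e-CBT gives results comparable with in-person CBT. If the comparison rests only on those with scores, a difference between arms in who is lost can hide a real difference or create a false one. Oversampling protects precision but does nothing about this. Comparing completers with withdrawals on demographics would not show whether their symptoms differed.

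**Working it through.** **Inputs from the article (Data Analysis, Participants).** 55 per arm, 110 in total; dropout up to 30%; alpha .05; power 0.95; two-tailed t tests. No dropout rate by arm, standard deviation or baseline PHQ-9 mean is given.

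**The plan's own figure.** Without a standard deviation, 55 per arm can be neither reproduced nor refuted. It can be back-solved from d = (1.960 + 1.645) × √(2/n), two-sided:

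- If 55 already includes the dropout allowance, about 38 per arm are analysed, and d = 3.605 × √(2/38) = 0.83. Power among completers is then as planned, and the issue is bias only.
- If 55 is the number needed for analysis, d = 3.605 × √(2/55) = 0.69. With 38 per arm, power falls from 0.95 to about 0.85.

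The article says that dropout was factored in, so the first reading is the natural one.

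**Participants lost to the comparison.** 0.30 × 55 = 16.5 per arm, which leaves 38.5 per arm. In total 0.30 × 110 = 33 are lost and 77 remain. This is a ceiling and applies to the later time points: someone who leaves after week 6 still has a week 6 score and enters that t test.

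**Bias of a completer comparison.** Let p be the dropout proportion in an arm and g the number of PHQ-9 points by which its dropouts do worse than its completers.

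- Full-arm mean = (1 − p) × completer mean + p × (completer mean + g) = completer mean + p × g.
- So completers make the arm look better by p × g, and the arm difference is biased by p₁g₁ − p₂g₂. With equal gaps this is g × (p₁ − p₂).

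The gaps and arm-specific rates below are assumptions, chosen to show the range.

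| Dropout, arm 1 vs arm 2 | Lost of 110 | Bias, g = 3 | Bias, g = 5 |
|---|---|---|---|
| 30% vs 30% | 16.5 + 16.5 = 33 | 0 | 0 |
| 30% vs 20% | 16.5 + 11 = 27.5 | 0.3 | 0.5 |
| 30% vs 10% | 16.5 + 5.5 = 22 | 0.6 | 1.0 |

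Equal dropout is not a guarantee: at 30% in both arms, gaps of 5 and 3 points give 0.30 × (5 − 3) = 0.6 point. The bias favours whichever arm has the larger p × g.

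**The case against.** Several stronger readings are tempting, and the document does not support them.

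- **That the two rules cannot both hold.** The intention-to-treat analysis is introduced as an addition, and a trial can report both analyses. The defect is wrong definitions and an unnamed primary analysis, not logical impossibility.
- **That no imputation rules out an intention-to-treat result.** It does not. A likelihood-based repeated-measures model analyses everyone enrolled without imputing. The article mentions regression over the four time points without saying whether it is longitudinal. What stands is that the t tests, the only method named for comparing the arms, use observed scores alone.
- **That everyone who withdraws lacks a score.** Questionnaires are collected through the platform (Outcome Evaluation), and nothing says that they stop when therapy stops. Withdrawal might also mean leaving the study, which Ethics and Data Privacy allows. The text does not settle which is meant.
- **That 33 participants are lost and the bias is also largest.** The 33 requires 30% dropout in both arms, where equal gaps give zero bias. The 30% versus 10% case loses 22.
- **That the error favours e-CBT.** No arm-specific dropout is given. The article's Introduction credits e-CBT with better adherence; if in-person dropout were higher, the same formula would work against e-CBT.

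It is also fair to say that an unseen analysis plan may hold more detail, and that intention-to-treat preserves no randomised balance here because participants choose their arm. Neither point repairs the text. The article fixes a rule and a description that are wrong as written, and self-selection makes it more important to keep everyone who entered each arm in view.

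**Conclusion.** The point holds as one of misstated rules. The article equates non-imputation with a per-protocol set, misdescribes intention-to-treat, and leaves the primary analysis open. Followed as written, the arm comparison at each time point rests on participants with observed scores.

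The loss is at most 33 of 110 at later time points, which assumes the 30% ceiling in both arms and no scores after dropout. The possible bias is 0.6 to 1.0 PHQ-9 point under the assumed 3 to 5 point gap with 30% versus 10% dropout, and zero with equal dropout and equal gaps. Its direction cannot be told from the document. The figures illustrate what is at stake; they do not predict this trial's result.

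**What to change.** 1. Delete the gloss that equates unimputed data with a per-protocol analysis, and describe intention-to-treat as all enrolled participants analysed in the arm they entered.
2. Name one primary set: all enrolled participants with a baseline score, in the arm they chose.
3. For the primary comparison, fit a likelihood-based repeated-measures mixed model to all observed week 6, week 12 and 6-month scores, keeping the planned adjustment for age and gender. This needs no imputation and is valid if data are missing at random given what the model includes.
4. Report per-protocol as supportive, with its adherence rule stated separately from the handling of missing scores.
5. Optionally, add a missing-not-at-random sensitivity analysis that varies the assumed outcome of dropouts in both arms, since the direction of any bias is unknown.

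The model in step 3 is one defensible choice among several; steps 1 and 2 are needed whichever model is used. The cost is wording and modest programming. No new data are needed.
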